## Abstract

**Background:**

Major Depressive Disorder (MDD) is a prevalent mental health condition with diverse treatment modalities. There is an unmet need in the treatment of major psychiatric disorders such as depression and naturalistic treatment options which are desirable particularly for chronic and severe courses of mental illness. In addition, there is an evidence gap for naturalistic treatment options for depression. This study compares the treatment effects and side effects of allopathic and ayurvedic treatments for MDD within a real-world setting. Allopathic approaches typically involve antidepressants and psychotherapy, while ayurvedic treatments may encompass herbal remedies, panchakarma, manual therapies, dietary modifications, yoga, meditation and lifestyle interventions.

**Methods:**

This six-month, naturalistic observational study will involve 105 adult participants (18–65 years) diagnosed with MDD according to DSM-5 criteria. Participants will be categorized to one of three groups: allopathic-only treatment (n=35), ayurvedic-only treatment (n=35), or a combination of both (n=35). Depressive symptom severity will be assessed as primary endpoint using primarily the MDRS, and secondarily HAMD and PHQ-9 scales at baseline, every 2 weeks until week 8, followed by monthly assessments until months 6. Secondary outcomes will exploratively include side effects (UKU, GASE, MARS), quality of life and daily functioning (WHOQoL-BREF, GAF, FAST) as well as general health measures (e.g. lab tests).

**Results:**

The study will compare changes in primary and secondary outcome measures across the three treatment groups over time (baseline vs. week 8, month 3 and month 6) using appropriate statistical models for longitudinal data (e.g., repeated measures ANOVA, mixed-effects models.

**Conclusions:**

This study will provide valuable real-world evidence on the comparative treatment effects and side effects of allopathic and ayurvedic treatments for MDD, informing clinical practice and future research directions in this area. Findings will contribute to a more nuanced understanding of treatment options for individuals with MDD.

## Highlights

There is an unmet need for evaluating naturalistic treatments of depressionThere is an urgent need to close evidence gaps for the evaluation of ayurvedic treatments for MDDSAFE compares allopathic and ayurvedic treatments for MDD within a real-world settingSAFE is a six-month study including 105 adults in three groups: allopathic, ayurvedic or a combinationSAFE will provide evidence on the comparative treatment effects and side effects of allopathic and ayurvedic treatments for MDD

## Introduction

1

### Background and rationale

1.1

Major Depressive Disorder (MDD), a debilitating mood disorder characterized by persistent sadness, anhedonia, and impaired functioning, poses a significant global health challenge (1). While the precise aetiology remains complex and multifaceted, converging evidence points to a dysregulation of neurobiological systems interacting with environmental and psychosocial factors (2). This interplay underscores the need for comprehensive treatment approaches that address both the biological and psychological dimensions of the disorder (3). Current treatment strategies primarily utilize allopathic and, increasingly, complementary and alternative medicine (CAM) approaches, such as Ayurvedic medicine (4). Despite a large use of the global prevalence of use of CAM/Ayurveda in depression, there is an urgent need to make naturalistic treatments available and to address evidence and clinical gaps in the treatment of depression.

Allopathic treatments for MDD predominantly focus on pharmacological interventions and various forms of psychotherapy (5). Pharmacological treatments primarily involve antidepressants, targeting neurotransmitter systems to alleviate depressive symptoms (6). Selective serotonin reuptake inhibitors (SSRIs), serotonin-norepinephrine reuptake inhibitors (SNRIs), tricyclic antidepressants (TCAs), and monoamine oxidase inhibitors (MAOIs) represent the main classes of antidepressants, although their efficacy varies considerably between individuals. Side effects, including sexual dysfunction, weight gain, and sedation, can limit treatment adherence and overall effectiveness (7). Furthermore, a substantial proportion of individuals exhibit treatment resistance, necessitating alternative or augmentation strategies (8). Psychotherapeutic interventions, particularly cognitive behavioural therapy (CBT) and interpersonal psychotherapy (IPT), play a crucial role in modifying maladaptive thought patterns, improving coping skills, and enhancing interpersonal relationships (9). These therapies often demonstrate comparable efficacy to antidepressants, particularly in preventing relapse.

Ayurvedic medicine, an ancient holistic system originating from India, offers an alternative and complementary approach to MDD (10). This system emphasizes the interconnectedness of mind, body, and spirit, aiming to restore balance through various interventions. These include herbal remedies (e.g., Ashwagandha, Brahmi etc.), dietary modifications tailored to individual constitution (Prakriti), lifestyle adjustments promoting holistic well-being, and mind-body techniques such as yoga and meditation (11). Ayurvedic treatment is well established in India. It is a holistic whole system approach that traditionally consists of specific components (Panchakarma, manual therapies Dietary Modifications, Herbal Formulations, Lifestyle Modifications, Sattvavajaya and Daiva-vyapasraya-cikitsa) that are integrated into a common treatment approach. There are special hospitals that specialize in such holistic treatment concepts. Patients can choose whether they want to be treated in an allopathic or an Ayurvedic hospital. While level A (e.g. meta-analysis and RCTs) and level B (evidence from at least one high-quality study or multiple moderate-quality studies) evidence studies and some smaller studies suggest the potential efficacy of Ayurvedic treatments in alleviating depressive symptoms (12–14), robust, large-scale randomized controlled trials comparing Ayurvedic treatment to allopathic treatments are relatively scarce (15). Understanding the mechanisms through which Ayurvedic treatment exert their effects on mood and related symptoms remains an area of active research.

This necessitates a more comprehensive understanding of the relative treatment effects, side effects and potential synergistic effects of integrating allopathic and Ayurvedic treatments for MDD. A comparative evaluation of these approaches is crucial for informing evidence-based clinical practice and optimizing therapeutic strategies for individuals experiencing this pervasive and debilitating disorder. This study aims to address this critical gap in the literature through observation and analysis of real-world outcomes of allopathic and ayurvedic treatment modalities for MDD.

### Hypothesis and objectives

1.2

Based on the published literature, we assume that allopathic and Ayurvedic treatments are equally effective in treating depression, both leading to improvements in symptom severity. Therefore, we do not expect any statistically significant difference in treatment effect between the treatment groups (between-group effect) in week 8. However, we hypothesize that both therapies will lead to an improvement in depression symptoms over a period of 8 weeks (within-group effect). The question is exploratory in nature due to the design and methodology.

This study will pursue the following scientific objectives:

Treatment Effect: To quantitatively compare the effect of allopathic and ayurvedic treatments (and their combination) in reducing the severity of depressive symptoms in MDD, as measured by validated rating scales (primary Montgomery-Åsberg Depression Rating Scale (MADRS), secondary Hamilton Depression Rating Scale (HAM-D) and Patient Health Questionnaire-9 (PHQ-9) at baseline, 8 weeks, 3 months and 6 months.Side Effects and Quality of Life: To compare the incidence, type, and severity of adverse events associated with allopathic and ayurvedic treatments using standardized adverse event reporting like Udvalg for Kliniske Undersøgelser Scale (UKU), General Assessment of Side (GASE) and Medication Adherence Report Scale (MARS). Furthermore, to assess differences in quality of life (QoL) and daily functioning between treatment groups using validated QoL instruments (e.g., WHOQOL-BREF) and functional assessment scales (e.g., Global Assessment of Functioning (e.g., Global Assessment of Functioning (GAF) and Functional Assessment Short Test (FAST).General Health Evaluation: To evaluate and compare changes in general health parameters (e.g., Body Mass Index (BMI), vital signs, relevant blood work indicators such as liver and kidney function tests, electrolytes, CRP, leukocytes, red blood cells, platelets, haemoglobin , haematocrit , red cell indices and TSH) across treatment groups over the study duration.

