### Trial design and study setting

2.1

This study employs a naturalistic observational (non-randomization) design, conducted within real-world clinical settings for a six-month period (see **Figure 1**) where the group assignment reflects patient preference and clinical practice in specialized hospitals. The study population comprises 105 adult participants. Participants will be observed in one of three treatment groups, each consisting of approximately 35 individuals, based on the treatment they receive (see **Figure 1**).

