### Sample size calculation and statistical analysis

2.9

We hypothesise that all treatment groups lead to a statistically significant reduction in symptoms of depression between baseline and week 8 (within group effect). We also hypothesize that the groups do not differ in terms of treatment success (between group effect). We performed a power analysis to calculate the sample size. With a sample size of N = 105 patients, an alpha error probability of 0.5 and a moderate effect size (0.5) (for change in symptoms of depression), we achieve a statistical power of >0.8. An effect size of 0.5 equates to a mean difference in the MADRS score between baseline and week 8 of 50%, which reflects a commonly accepted clinical response measure in depression studies. In practise , this would mean a reduction of 15 points on the MADRS scale from 30 points at baseline to 15 points at week 8. Such a kind of reduction has been seen in other interventional studies in depression.

Data analysis will be conducted by the team at the Department of Psychiatry, University of Münster. The primary and secondary outcome measures will be analysed using an intention-to-treat (ITT) and exploratory approach. We will focus on specialized analyzation for longitudinal data. In addition, we will correct for confounding variables in all analyses where significant differences arise between the groups.

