The choice of statistical test will depend on the nature of the data and the specific research question. For continuous outcome variables (e.g., scores on depression rating scales, quality of life scores, continuous physiological measures), Analysis of Variance (ANOVA) or independent samples t-tests will be used to compare means between the three treatment groups (Ayurvedic-only, Allopathic-only, and Combination). *Post-hoc* tests (e.g., Tukey’s HSD, Bonferroni correction) will be employed if significant differences are found between groups to determine which specific groups differ significantly. For categorical outcome variables (e.g., presence or absence of adverse events, categorical measures of quality of life, treatment adherence categories), Chi-square tests or Fisher’s exact tests (for small sample sizes) will be used to compare proportions between treatment groups. Given the repeated measures design (baseline, 8 weeks, 3 months, 6 months), appropriate statistical models for longitudinal data (e.g., repeated measures ANOVA, mixed-effects models) will be used to analyse changes in outcome measures over time within each treatment group and to examine the interaction effects between treatment group and time. This will allow for a more powerful examination of treatment effects and the assessment of treatment response trajectories. Strategies to address missing data will be carefully considered and documented. In addition to p-values, effect sizes (e.g., Cohen’s d) and 95% confidence intervals will be reported for all significant findings. All statistical analyses will be performed using appropriate statistical software packages (e.g., SPSS, R).

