### Limitations

3.2

While the real-world study has advantages for translation and generalizability to clinical practice , this comes with limitations such as potential confounding, selection bias, and heterogeneity of Ayurvedic and allopathic interventions, which could affect internal validity. In this context, it should be noted that the choice of treatment depends strongly on the preferences of the patients and the approach of the treating clinic and physicians, even though participatory decision-making processes are particularly important with regard to the treatment of psychiatric patients. Even though a wait-list control condition or a no-intervention arm would provide valuable data and improve the interpretability of the findings, this would not be ethically justifiable in our sample.

Moreover, the generalizability is limited to comparable settings in India. It should be noted that the exclusion of suicidality and substance abuse leads to a small but ethically necessary restriction of the naturalistic cohort.

Furthermore, the approach of a multimodal and routine (non-randomised) intervention program in both Ayurvedic and allopathic treatment arms have the potential disadvantage that no causal inferences can be made about specific effects of individual components of the treatment. However, we would like to emphasize that a more holistic approach to treating depression reflects clinical reality and carries a higher weight for translation into routine settings.

This study is designed to determine whether the applied treatments are effective in producing changes in the dependent variables. However, it is not intended to explain how or through which mechanisms the treatment leads to successful outcomes. Addressing this question would require a research design that captures the complexity of real-world settings with greater ecological validity (e.g., alternative approaches such as the integrative single-case design) (41).

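### No between-group difference is stated as a hypothesis, but only difference tests are named, no similarity margin is given, and intervals are promised only for significant findings

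*Protocol article*

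**What the plan says.** Section 1.2 starts from a premise drawn from the literature: "we assume that allopathic and Ayurvedic treatments are equally effective in treating depression, both leading to improvements in symptom severity". From it the article concludes: "Therefore, we do not expect any statistically significant difference in treatment effect between the treatment groups (between-group effect) in week 8". Section 2.9 turns this into a hypothesis: "We also hypothesize that the groups do not differ in terms of treatment success (between group effect".

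For continuous outcomes, section 2.9 says "Analysis of Variance (ANOVA) or independent samples t-tests will be used to compare means between the three treatment groups", with post-hoc tests if the overall result is significant. It also names repeated-measures ANOVA or mixed models with a group-by-time interaction. All of these test for a difference. No equivalence or non-inferiority test and no margin appears, and effect sizes and 95% CIs are promised only for findings that reach significance.

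The within-arm hypothesis in 2.9 is: "We hypothesise that all treatment groups lead to a statistically significant reduction in symptoms of depression between baseline and week 8 (within group effect". Section 3.2 concedes that a wait-list or untreated arm would have made the findings easier to interpret, yet also says: "This study is designed to determine whether the applied treatments are effective in producing changes in the dependent variables".

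**The concern.** The between-group research hypothesis is the null hypothesis of the tests that are to examine it. Such a test can count against the hypothesis but cannot support it. A non-significant result arises when the arms are alike and also when the study is too small to separate them, and only an interval tells these two cases apart. Under the stated reporting rule, the expected result is the one for which no interval is promised.

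The risk is that a moderate inferiority of one arm, in patients with moderate or severe depression, reaches readers as an absence of difference with nothing to show how wide the uncertainty is. The within-arm half has a smaller problem. A fall from baseline without an untreated comparator is a change under treatment, and the quoted sentence in 3.2 claims more than that.

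**Working it through.** **Inputs from the article.** Total size: "With a sample size of N = 105 patients" (2.9). Allocation: "Participants will be observed in one of three treatment groups, each consisting of approximately 35 individuals, based on the treatment they receive" (2.1). Effect size 0.5, described as a change from baseline to week 8, with power above 0.8 (2.9). Alpha is printed as 0.5 and is read here as 0.05; that is my assumption and a separate point.

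**Inputs that are assumed.** The article gives no SD for MADRS, no margin and no between-arm difference of interest. I take SD 10 (range 8 to 12), a true difference of 4 points, an illustrative margin of 5 points, and no dropout.

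**Step 1. Which test the stated power belongs to.**
- Paired test within one arm, n = 35, d = 0.5: noncentrality 0.5 × √35 = 2.96, power 0.82. This reproduces the stated figure.
- Two-sample test, 35 v 35, d = 0.5: noncentrality 0.5 × √(35/2) = 2.09, power 0.54.
- Three-arm ANOVA: 0.61 at f = 0.25. It passes 0.8 at f = 0.5 (0.997), but the text ties 0.5 to a change from baseline, not to Cohen's f.

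So the power statement fits the pre-post test, not the pairwise comparison between arms.

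**Step 2. What a null result would leave open.** SE of a difference = SD × √(2/35). 95% half-width = t(0.975, 68) × SE, with t = 1.995. The last column uses noncentrality 4/SE.

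| SD | SE | 95% half-width | P(non-significant), true difference 4 |
|---|---|---|---|
| 8 | 1.91 | 3.8 | 46% |
| 10 | 2.39 | 4.8 | 62% |
| 12 | 2.87 | 5.7 | 72% |

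**Step 3. Where this stops being true.** Chance of a non-significant pairwise result by standardised difference: d = 0.3, 76%; d = 0.4, 62%; d = 0.5, 46%; d = 0.8, 9%. Without multiplicity correction, missing is the likelier outcome only below about d = 0.5.

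**Step 4. Could similarity be shown with this sample?** With no true difference, the chance that a 95% CI lies inside ±5 is approximately 2Φ(5/SE − 1.96) − 1. At SD 10 this is 2Φ(2.09 − 1.96) − 1, about 10%. With the more lenient 90% CI (two one-sided tests at 0.05), simulation gives 33% at SD 10, 66% at SD 8 and 8% at SD 12.

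**Step 5. The within-arm half.** Suppose natural course alone gave a 5-point fall, and the SD of change equals the SDs above (both assumptions). One arm is then significant with probability 0.95, 0.82 and 0.67 at SD 8, 10 and 12. For all three arms, cubing gives 0.85, 0.55 and 0.30. With no mean change at all, significant improvement has probability 2.5% per arm.

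**The case against.** A reader might infer that the study plans to declare the treatments equal on the strength of p > 0.05. The article does not say so. Equal effectiveness is a premise in 1.2, non-significance is an expectation drawn from it, and the stated objective is a quantitative comparison. Sections 1.2, 2.7 and 2.9 use the word exploratory, and section 4 calls the findings hypothesis-generating and disclaims definitive clinical recommendations. This stands, and it lowers the severity.

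A reader might also infer that both hypotheses would probably be confirmed even if the treatments did nothing. That is not supported either. It needs a natural improvement of roughly half an SD or more, which the article does not quantify. Step 5 shows that significance in all three arms is then anything from likely to unlikely, and more noise makes it less likely. Section 3.2 already concedes confounding, selection bias and the lack of an untreated arm, and the quoted sentence there serves mainly to contrast whether change occurs with how it occurs.

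The calculation is for an unadjusted comparison. With an assumed baseline correlation of 0.5, adjustment cuts the residual SD by √(1 − 0.25) = 0.87, and the miss rate at SD 10 falls from 62% to about 52%. The size changes but not the conclusion.

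An analysis plan that is not shown may hold interpretation rules. The hypothesis, the tests and the reporting rule are nevertheless all stated here, and they do not fit together.

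**Conclusion.** The mismatch is real and should be fixed. A hypothesis of no difference is paired only with difference tests, no margin is given, and intervals are promised only for significant results. At 35 per arm the likely null result would be compatible with differences of about 4.8 MADRS points either side of the estimate (3.8 to 5.7 for SD 8 to 12), and a true 4-point difference would be missed 62% of the time (46 to 72%).

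These figures rest on an assumed SD, an assumed difference, two-sided alpha 0.05 and complete data. They do not extend to large differences, which would usually be detected. The within-arm part comes down to the hypothesis wording in 2.9 and one sentence in 3.2 that claims more than an uncontrolled change can show. The exploratory label limits the harm but does not make the tests fit the hypothesis.

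**What to change.** - **2.9, reporting:** give the baseline-adjusted week-8 MADRS differences A−B, A−C and B−C with 95% CIs, whether or not they are significant.
- **1.2 and 2.9, hypothesis:** replace the no-difference hypothesis with estimation of these differences, and state that non-significance will not be read as equal effectiveness.
- **Use of the word *comparable*:** allow it only if the 95% CI lies inside a margin that the sponsor fixes and justifies before seeing data. Otherwise report *inconclusive*.
- **Within-arm results:** describe them as change under treatment, and reword the 3.2 sentence so that it no longer claims to determine whether the treatments are effective.

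The cost is wording and a little extra reporting, with no change to sample size, visits or data collection. The downside is that the between-group conclusion will probably be *inconclusive*. With an illustrative 5-point margin, SD 10 and no true difference, the chance of *comparable* is only about 10%.

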## Methods

2

### Trial design and study setting

2.1

This study employs a naturalistic observational (non-randomization) design, conducted within real-world clinical settings for a six-month period (see **Figure 1**) where the group assignment reflects patient preference and clinical practice in specialized hospitals. The study population comprises 105 adult participants. Participants will be observed in one of three treatment groups, each consisting of approximately 35 individuals, based on the treatment they receive (see **Figure 1**).

**Figure 1 f1:**
[figure not shown]
Flowchart of the study visits over time.

Arm A: Allopathic-Only Treatment: Participants in this arm will receive standard allopathic care, including antidepressant medication and psychotherapy as determined clinically appropriate.Arm B: Ayurvedic-Only Treatment: Participants in this arm will receive treatment exclusively with ayurvedic modalities.Arm C: Combination Treatment: This arm permits the integration of both ayurvedic and allopathic treatments, reflecting the increasing trend toward integrated care approaches.

At week 8 participants will be given the opportunity to reevaluate their treatment. This allows for a more patient-centred approach and accommodates individual responses to treatment. This enhances the study’s relevance to real-world clinical practice , where treatment decisions often involve adaptations based on ongoing assessment.

